**Fig. 1 Fig1:**
[figure not shown]
Study design flow chart

The SOFTLY trial will test the hypothesis that EOF, which will be initiated on POD1, is not inferior to DOF on POD4 for patients undergoing TLRG in terms of anastomotic leakage rate.

A complete checklist of items according to SPIRIT 2013 [22] is provided in Additional file 1.

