### Study endpoints

The primary endpoint will be the percentage incidence of anastomotic leakage after TLRG. We will determine whether or not EOF at POD1 is non-inferior in terms of the occurrence of post-operative fistulas, including anastomotic leakage. Anastomotic leakage will be defined as the breakdown of the connection and subsequent leakage of digestive system fluid from a surgical anastomosis of digestive system structures. If anastomotic leakage is clinically suspected post-operatively, digestive tract radiography will be performed to diagnose the leak. Usually, sufficient abdominal drainage is the most effective treatment.

The secondary endpoints are post-operative recovery and nutritional status, as follows: (1) post-operative complications (n) at 30 days according to the Clavien Dindo classification, which include incisional infection, abdominal abscess, intraperitoneal hemorrhage, anastomotic bleeding, postoperative intestinal obstruction, pancreatitis, pulmonary complications, and others organ complications; (2) the time of first flatus and defecation (day); (3) post-operative length of stay (day); and (4) hospitalization costs (Yuan).

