### Sample size estimate

Based on the data from the CLASS-01 study [21], the anastomotic leakage rate in this trial is defined as 1.9%, and previous RCTs involving open gastrectomy concluded that there were no significant differences between EOF and traditional oral feeding (DOF) with regard to the risk for anastomotic leakage [19, 24]. To verify that EOF is non-inferior regarding the anastomotic leakage rate after laparoscopic radical gastrectomy, we designed a non-inferiority test with a non-inferiority margin of 5% (α = 0.05, β = 0.20, and a power of 80%). Considering both clinical and statistical considerations like intolerance of enteral nutritions, therefore, no less than 160 participants (80 participants in each group) will be required. Allowing for a 20% drop-out and withdrawals before trial completion, we decided to recruit a total of 200 participants (100 participants in each group) [21].

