### Statistical analysis

The intention-to-treat principle will be applied in all analyses with an assumed drop-out rate. Normally distributed continuous variables will be described as the mean with corresponding SDs, and non-normally distributed or categorical variables will be described as medians with the corresponding range or percentages and frequencies. Normally or non-normally distributed continuous data will be compared by Student’s *t*-test or the Mann–Whitney U test, and the chi-square test and Fisher’s exact test will be used to compare categorical variables, as indicated. With the exception of the primary outcome, secondary outcomes, such as post-operative complications, time of first flatus and defecation, and post-operative length of stay, will also be compared. The potential risk factors for intolerance of EOF and post-operative complications will be identified using a multivariate analysis. A blinded statistician will analyze all of the data using a two-sided *P* value < 0.05 to represent statistical significance.

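### The Statistical analysis section sets only two-sided difference tests and gives no margin-based rule for leakage, so it does not carry through the 5% non-inferiority design

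*Protocol article*

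**What the plan says.** All references are to the protocol article.

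- **Hypothesis (Methods/design, text after Fig. 1):** early oral feeding (EOF) on postoperative day 1 "is not inferior to DOF on POD4 for patients undergoing TLRG in terms of anastomotic leakage rate". DOF is delayed oral feeding. Treatment protocols calls the trial confirmatory.
- **Endpoint (Study endpoints):** "The primary endpoint will be the percentage incidence of anastomotic leakage after TLRG". It is a binary outcome, and the next sentence again frames the question as non-inferiority.
- **Design (Sample size estimate):** "the anastomotic leakage rate in this trial is defined as 1.9" per cent, and "we designed a non-inferiority test with a non-inferiority margin of 5" per cent, with "α = 0.05, β = 0.20, and a power of 80" per cent. The result is "no less than 160 participants (80 participants in each group) will be required", raised to 100 per group for 20% drop-out. Neither the sidedness of alpha nor the scale of the margin is given.
- **Analysis (Statistical analysis):** continuous data get a t-test or Mann–Whitney test. For the rest, the chi-square test and Fisher's "exact test will be used to compare categorical variables, as indicated". The closing rule is "A blinded statistician will analyze all of the data using a two-sided" P value below 0.05.

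The Statistical analysis section contains no margin, no confidence limit for the leakage difference and no separate decision rule for the primary endpoint.

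**The concern.** The design and the analysis rule address different null hypotheses. The design needs to reject an excess of leaks at or beyond the margin. The chi-square and Fisher tests reject equality of the two rates. Failing to reject equality is not evidence that the excess is below the margin, least of all when few events are expected: 1.9% of 100 is about 2 leaks per arm if the rates are equal.

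Leakage is a safety endpoint and the basis of the trial's main conclusion. An analyst who follows the Statistical analysis section literally gets a P value that can neither support nor refute the stated hypothesis. One who follows the Sample size estimate section must depart from a rule written for all of the data.

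**Working it through.** **Inputs.** DOF rate 1.9%, margin 5%, alpha 0.05, power 80%, 80 evaluable and 100 recruited per arm (Sample size estimate). Two-sided P < 0.05 with chi-square or Fisher (Statistical analysis). Assumptions: the margin is absolute (5 percentage points), and the two true rates are equal for the sample-size formula.

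**1. The plan's own figure.** With equal rates p and margin δ, n per arm = 2p(1−p)(z₁₋α + z₀.₈₀)²/δ².
- One-sided 0.05: 2 × 0.019 × 0.981 × (1.645 + 0.842)² / 0.05² = 0.03728 × 6.183 / 0.0025 ≈ 92.2, so 93.
- One-sided 0.025: 0.03728 × 7.849 / 0.0025 ≈ 117.04, so 118.

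The stated 80 matches neither. The drop-out step does reproduce: 80/(1 − 0.20) = 100. The shortfall is a separate matter, and this point does not depend on it. Both 80 and 100 per arm are carried below.

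**2. True rates at the margin.** EOF = 1.9% + 5% = 6.9%; DOF = 1.9%. For each pair of leak counts (x, y), weight by Bin(x; n, 0.069) × Bin(y; n, 0.019) and sum over the pairs that meet each criterion.

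| Outcome | 80 per arm | 100 per arm |
|---|---|---|
| Fisher, two-sided P ≥ 0.05 | 82% | 73% |
| Chi-square (uncorrected), two-sided P ≥ 0.05 | 69% | 61% |
| Score test of 5-point margin passes, one-sided 5% | 3.8% | 4.6% |
| Score test of 5-point margin passes, one-sided 2.5% | 1.6% | 2.0% |
| Wald limit below 5 points, one-sided 5% | 9.2% | 7.1% |

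The first two rows are probabilities of a non-significant difference test. The last three are false declarations of non-inferiority. The Wald row shows why the interval method matters: its error rate exceeds the nominal 5%.

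**3. One data set.** Take 7 leaks in 100 (EOF) against 1 in 100 (DOF). The smallest expected count is (7 + 1)/2 = 4, so under the usual expected-count-of-5 convention (an assumption; the article states none) Fisher applies, giving P = 0.065. The observed excess is 6.0 points, already beyond the margin (Wald 95% interval 0.6 to 11.4, for description only). At 80 per arm the same counts give P = 0.064 and an excess of 7.5 points (0.8 to 14.2). The difference test is non-significant, yet non-inferiority is clearly not shown.

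**The case against.** **The Sample size estimate section does name a non-inferiority test.** A reader might infer that the 5% question will never be tested. The document does not support that: the margin, alpha and power are stated there, the hypothesis and endpoint sections repeat the aim, and an unseen statistical analysis plan could apply the test. The choice of interval method is also commonly left to such a plan. What remains is that the Statistical analysis section states a rule for all of the data, and that rule conflicts with the design. This is a contradiction in the text, not an omitted detail.

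**Nothing says that non-significance will be taken as safety.** A reader might infer it because the Sample size estimate section relies on earlier trials that found no significant leakage difference, and the Discussion looks ahead to early feeding proving as safe as delayed. Neither is a decision rule. The 61–82% figures are chances of a non-significant result, and become wrong-conclusion rates only if non-significance is misread in that way.

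**One sentence may set the primary outcome apart.** The Statistical analysis section says secondary outcomes will also be compared with the exception of the primary outcome. The likelier meaning is *in addition to* the primary outcome. Even read as an exclusion, it leaves leakage with no stated test.

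**The difference tests are not blind to harm.** At the margin with 100 per arm they are significant in 27% (Fisher) to 39% (chi-square) of trials. At a true EOF rate of 10%, Fisher is non-significant in about 40%. The choice of test also matters: 9 against 2 leaks per 100 gives Fisher P = 0.058 but chi-square P = 0.030, and with a smallest expected count of 5.5 chi-square would usually be chosen and would flag harm. It would therefore be wrong to call non-significance almost certain when early feeding is worse. None of this turns a difference test into a test of the margin.

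**Conclusion.** The point holds and should be corrected before the final analysis. The Statistical analysis section does not carry through the non-inferiority hypothesis and 5% margin set elsewhere in the article. With true rates at the margin, its tests are non-significant in 61–73% of trials at 100 per arm and 69–82% at 80 per arm, against about 4–5% false passes for a one-sided 5% score test of the margin.

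The figures assume an absolute margin, a 1.9% control rate and no interim looks. The conflict itself does not depend on them. The conclusion stops at the written rule; it does not claim that the investigators will ignore the margin or misreport a non-significant result.

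**What to change.** In the Statistical analysis section (and the statistical analysis plan, if one exists), state that:

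1. The primary analysis is the risk difference in leakage, EOF minus DOF, with a score-type confidence interval suited to few events (for example Miettinen–Nurminen/Farrington–Manning, or Newcombe), not a Wald interval.
2. Non-inferiority is declared only if the upper limit is below 5 percentage points, at a stated one-sided alpha consistent with the Sample size estimate section. That section should state the sidedness of its 0.05 and that the margin is absolute.
3. Two-sided P < 0.05 difference tests apply to secondary outcomes only.

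**Cost.** This is a wording change with no extra data or patients. The article reports 102 of 200 recruited at submission, so on that status the change could precede the final analysis. The downside is that a score interval is less favourable than a Wald interval. With both true rates at 1.9% and a one-sided 2.5% level, exact enumeration gives a pass in 38% (score) against 67% (Wald) of trials at 80 per arm, and 49% against 76% at 100 per arm. At one-sided 5% the score test passes in 54% and 72%. The choice of alpha should be made with these figures in view.

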## Discussion

Factors such as fasting, parenteral nutrition only, stress response after gastrointestinal surgery, and perioperative use of antibiotics can result in inhibition of secretion of saliva and gastrointestinal fluid, impair gastrointestinal motility and intestinal mucosal barrier function, and disrupt the gut microbiome. The use of a traditionally applied nil-by-mouth strategy is often adopted because EOF might lead to a digestive tract fistula or secondary bowel obstruction due to increased intestinal pressure [10, 25]; however, there is no evidence to support this theory. In spite of lacking robust data, the ESPEN and ERAS guidelines after gastrectomy recommend early initiation of oral intake as the preferred route for nutrition.

In recent years, EOF as a nutrition route in accordance with physiological needs after open gastrectomy has been shown to be associated with a decreased hospital LOS without improving the anastomotic leakage rate. Limited data are available for laparoscopic radical gastrectomy.

The proposed study is based on research following open gastrectomy to assess the safety and feasibility of EOF after laparoscopic radical gastrectomy. Under the guidance of ERAS, whether or not EOF will lead to significant benefits will also be assessed compared with DOF.

If EOF after laparoscopic radical gastrectomy proves to be as safe as DOF, additional multicenter studies will be conducted. The effects of content and food intake of EOF on post-operative benefits should be explored in a corollary study, striving to designate EOF as a new nutritional treatment after gastrectomy.

## Trial status

Enrollment for this study is ongoing at the time of manuscript submission. Currently, the trial has already recruited 102 patients.

## Data Availability

Not applicable.

## Abbreviations

AE: Adverse event
BMI: Body mass index
DOF: Delayed oral feeding
ECOG: Eastern Cooperative Oncology Group
EOF: Early oral feeding
ESPEN: European Society for Parenteral and Enteral Nutrition
LOS: Length of stay
NRS2002: Nutritional Risk Screening 2002
RCT: Randomized controlled trial
